**3.4 Analysis of the population**

The primary endpoint will be analyzed according to the intention-to-treat principle.

Per protocol analysis of actual treatment will be performed.

**4. Randomization and data management**

**4.1 Randomization**

The participants will be randomized using online randomization tool provided by TrialPartner.

**4.2 Data management**

The study is approved by the Norwegian regional ethics committee (MREK) and “personvermombudet” from “Datatilsynet”.

The OCT images will be coded and all patient identification will be removed. Images will be stored in a digital storage unit. The core lab will not be blinded to which treatment arm the images belong, as the stents have different appearance on OCT images. The analysis will follow the “Consensus standards for Acquisition, Measurement, and Reporting in Intravascular Optical Coherence Tomography Studies”.

Data will be stored and analyzed according to Ethical committee guidelines.

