**Rationale**

The pathological analysis will be compared to pre-,post- PCI and follow-up OCT readings to establish if composition, size and age predicts residual thrombus pre PCI as measured stent result after PCI and primary and primary endpoint at follow-up as measured by OCT. These results will be published in a separate substudy paper.

- 1. **Study goals and objectives**

Study goal is to compare the performance of the Absorb bioresorbable scaffold with a metallic drug eltuting stent in the STEMI patient.

Hypothesis is that a bioresorbable vascular scaffold (BVS) is non-inferior to standard of care, eg. direct stenting with metallic DES, using direct stenting after thrombus aspiration.

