### OPTIS St. Jude Medical OCT system will be used. Pre PCI: (after predilatation) OCT imaging catheters will be inserted and advanced to a position distal to the lesion and acquisition of the lesion will be performed at 36 mm/s (OPTIS). Final result acquisition: the OCT imaging catheters will be inserted and advanced to a position with acquisition start at least 5 mm distal to the distal stent edge. Pullback speed 20 mm/sec covering the. If target segment is longer than 53 mm then an additional pullback is performed covering entire target area. Final result is acquired by OCT. Flushing is performed by automated injector or manual injection. Iomerone contrast will be used for flushing. In case of difficult flushing, a larger guiding catheter or a more co-axial position of the guiding catheter is recommended. OCT files from baseline, follow-up and events (pre-intervention) should be submitted in RAW format to the Interventional Imaging Core Laboratory at Aarhus University Hospital via the study organization. Flushing for 3 seconds of the OCT imaging wire immediately before each pullback is mandatory

Careful evaluation of acquired pullback before finalizing procedure:

- Blood in catheter?
- Insufficiently flushed vessel?
- Target area acquired?
- SB ostium visible? (excess wire shadow?)

REPEAT PULLBACK IF QUALITY IS INSUFFICIENT

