**2.3 Treatment step-by-step**

Before arrival et cath lab, loading with acetylic salisylic acid and one of the antiplatelet agents clopigrogel/pragusgrel/ticagrelor is mandatory. Heparin or bivalirudin at start of procedure. After angiography and confirmation of presence of thrombus GpIIb/IIIa inhibitors are administered at operators discretion.

After thrombus aspiration with TIMI flow 2 or more the patient will be asked to participate in the study. Oral consent witnessed by staff non-affiliated with the study will be obtained.

OCT scan will be performed after 0.2 mg intracoronary nitroglycerine for sizing and lesion evaluation. The patient is then randomized into one of two arms in a 1:1 distribution:

1. Direct stenting with everolimus eluting stent
2. Direct stenting with bioresorbable stent

Direct stenting is the preferred method of implantation to keep procedure as short and simple as possible. Predilatation will not considered protocol violation if deemed necessary by operator. After stenting and post dilation at operator’s discretion, a second OCT will be performed. Any further post dilatation will be performed at operator’s discretion. A final OCT will be done if further postdilatation is performed. 0.2 mg intracoronary nitroglycerine is administered before each OCT scan.

Patient will be asked to sign an informed consent after the procedure (<24 hrs).

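### Protocol 4.2 leaves the OCT core lab unblinded because the stents look different, but this reason does not cover the stent-free pre-PCI scan, which could be read blind at almost no cost

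*Protocol*

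**What the plan says.** Protocol 4.2 (Data management) deals with blinding of the OCT core lab in two sentences. The first covers identity: "The OCT images will be coded and all patient identification will be removed". The second covers treatment arm: "The core lab will not be blinded to which treatment arm the images belong, as the stents have different appearance on OCT images". It names no time point and makes no exception.

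Section 2.3 gives the order of events at the index procedure. After aspiration and oral consent, "OCT scan will be performed after 0.2 mg intracoronary nitroglycerine for sizing and lesion evaluation". Next, "The patient is then randomized into one of two arms in a 1:1 distribution". Only then is the device implanted: "After stenting and post dilation at operator’s discretion, a second OCT will be performed".

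Section 2.2.12 (OCT acquisition technique) says what goes to the core lab: "OCT files from baseline, follow-up and events (pre-intervention) should be submitted in RAW format". Section 2.2.11 says the analysis there is done off line.

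Pre-PCI readings have a planned use. The rationale for the thrombus analysis asks whether thrombus "composition, size and age predicts residual thrombus pre PCI", and also relates the histology to the post-PCI stent result and to the primary endpoint at follow-up. Section 3.2 lists OCT measures of the vessel and the lesion, before and after PCI, directly after the logistic regression for independent predictors.

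**The concern.** The core lab's blinding status is fixed by one reason, and that reason fails for one class of scan. The pre-PCI image contains no device, so nothing in it can reveal the arm. A reader could learn the arm only from a label or from seeing the same patient's later runs.

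A measurement taken before randomisation cannot be changed by the device. A systematic difference between arms in such a measurement can come only from chance or from the way it was read. Blind reading removes the second source. If it is given up, two things are at stake:

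- A reader who knows the arm may shade lesion severity or vessel size by device. Any analysis that adjusts for these measures would carry that shading.
- A reader who knows the 12-month result may judge the baseline lesion or residual thrombus worse where the result was poor. That would inflate the apparent predictive value of the baseline finding.

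**Working it through.** **The plan's own figure.** Section 3.3 gives SD 1.39 mm², margin 0.72 mm², alpha 0.05 and power 0.85, with 54 patients per group. Taking alpha as one-sided and the true difference as zero:

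n = 2 × 1.39² × (1.645 + 1.036)² / 0.72² = 2 × 1.9321 × 7.188 / 0.5184 = 53.6, rounded up to 54.

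The figure is reproduced. None of its inputs concerns the pre-PCI scan, so nothing below changes it. The rest of the check compares sections.

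**Step 1: which scans does the reason in 4.2 cover?**

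| Scan | Source | Relation to randomisation | Device in the image | Reason in 4.2 applies |
|---|---|---|---|---|
| Pre-PCI | 2.3, 2.2.12 | before | none | no |
| Post-stent, and final if repeated | 2.3 | after | yes | yes |
| 12-month | 2.6 | after | yes (section 1 puts full resorption at 2 to 3 years) | yes |
| Event, before re-intervention | 2.2.12, 2.6 | after | yes | yes |

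Only the first row falls outside the stated reason.

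**Step 2: is the timing of the first row secure?** Section 2.2.12 describes the scan as follows: "Pre PCI: (after predilatation) OCT imaging catheters will be inserted and advanced to a position distal to the lesion". Section 2.3 places the scan before randomisation and mentions predilatation only later, as something permitted at the operator's judgement. The two sections must be reconciled. For this point the difference does not matter, because the scan is stent-free on either reading.

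**Step 3: can the arm be known at the time of reading?** The scan precedes allocation, but its measurement does not. Files are transferred and analysed off line, when the patient already has an arm. The coding in 4.2 removes identity and is not said to remove arm. The protocol sets no reading order and no separate code for pre-PCI files. So the arm may be known, as may the follow-up result if files are read together after 12 months. The document does not say that either happens.

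**Step 4: which analyses use the scan?**

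- *Primary endpoint (2.2.6).* The index scores strut coverage, malapposition, neointima or diameter stenosis, and lumen outside the stent. All need a device in the image. The pre-PCI scan contributes nothing.
- *Sizing variable (3.3).* Minimum flow area is taken from a trial with OCT at follow-up, so it does not depend on the pre-PCI scan.
- *Predictor analysis (3.2).* The OCT measures stand in a sentence without a verb, directly after the regression. That they are candidate predictors is inferred from position.
- *Thrombus substudy.* Residual thrombus before PCI is one of three OCT quantities to be related to histology.
- *OCT thrombus burden (2.2.7.1).* It is listed without a time point, so the pre-PCI scan may or may not be included.

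**Step 5: size.** The protocol gives no reader variability and no expected shift between blinded and unblinded readings, so a bias cannot be calculated. What can be stated is the reach: a pre-PCI acquisition is planned in each of the 120 patients.

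**The case against.** The strongest reply is that the sentence in 4.2 carries its own limit. It says why blinding fails, and that reason can only concern images with a stent. On this reading the sponsor never meant to unblind the pre-PCI scan. Nothing says that pre-PCI files carry an arm label or that readers open the stented runs first, and reading order is often set in core-lab procedures that are not shown. This stands in part: that the waiver covers every image follows from an unqualified sentence and is not stated in so many words. But the protocol does fix the blinding status, and no sentence keeps the pre-PCI scan blind. If the narrow meaning was intended, one added clause settles it.

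Four stronger inferences are tempting, and the document does not support them:

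- *That the primary comparison is compromised.* The Healing Index items are read on stented runs, where the protocol's reason holds.
- *That pre-PCI covariates certainly enter the regression.* The sentence in 3.2 is a fragment and does not say so.
- *That knowing the device by itself biases the thrombus substudy.* That substudy relates histology to OCT and does not compare arms. The more plausible route is knowledge of the follow-up result.
- *That OCT readers also see histology, clinical events or site.* Histology and OCT analysis are done at different institutions, and no section says that readers receive any of the three.

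**Conclusion.** The point holds in a limited form. Section 4.2 leaves the core lab unblinded on a ground that does not reach the pre-PCI scan, and nothing else in the protocol protects that scan's readings. The consequence is confined to secondary material: vessel and lesion measures before PCI, residual thrombus, and whatever analyses use them. The primary endpoint, the 54 per group, alpha and power are unaffected. The magnitude of any bias is unknown.

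The conclusion rests on three assumptions: that the unqualified sentence in 4.2 applies to all OCT files sent to the core lab; that the OCT measures in 3.2 are meant for the predictor analysis or another reported analysis; and that no document outside the protocol already imposes blind reading of the pre-PCI pullbacks. If the last is false, a cross-reference in 4.2 is enough. The point is a low-priority improvement, worth making because it costs so little.

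**What to change.** In 4.2, limit the statement on unblinded reading to pullbacks that show a device: post-stent, follow-up and event runs. Add that pre-PCI pullbacks go to the core lab under a separate code without the arm, and that their readings are completed and locked before the same patient's stented and follow-up runs are opened. State the timing of the pre-PCI scan consistently in 2.2.12 and 2.3.

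The cost is a second code per patient and a reading-order rule at the core lab. No extra reader, procedure or patient is needed. The matched cross-sectional item of the Healing Index is not hindered, because the extra-stent lumen it measures can be assessed only on runs that show the device.

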**5 Quality assurance**

Clinical Events Comitee (CEC) by [name] (leader) and [name] (Feiring-LHL klinikkene) will assess all Serious Adverse Events (SAE), the primary endpoint and the clinical secondary endpoints.

To be reported as SAE are unexpected clinical happenings leading to:

Life threatening incidences

Prolonged hospitalization

Persistant or significant disability

In addition:

All death

All incidences of contrast nephropathy

All incidences of loss of flow in coronary vessels after stenting (no reflow and side branch occlusions).

All cases of stent failure, eg stent thrombosis, stent fracture, loss of stent.

All bailout stenting with DES in the BVS group.

Expected clinical events not related to the stents will not be reported, such as congestive heart failure (including shock), arrhythmias, rehospitalization without evidence of restenosis or stent thrombosis.

An independent Data Safety Monitoring Board (DSMB) committee led by [name] (Amsterdam Medical Center) will evaluate safety after inclusion of 40 patients within 30 days of inclusion.

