**2.2.5 Schedule of event registration**

Clinical events will be note at index procedure. Participants will be contacted by telephone after 3 and 6 months, and clinical control as outpatient at 12 months with MCST and echocardiography.

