**11.2 Risk, side effects, advantages and disadvantages in participating in the study**

The extra risk for the patient during the index procedure is minimal as the both OCT and the stents used in both arms are considered safe. The primary procedure time will be about 10-20 minutes longer.The BVS has lower structural strength, but has the advantage of leaving behind now foreign object in the body after resorbtion.

The extra risk is primarily related to the control angiography. Major adverse effects are related to bleeding and hematoma at access point. More serious events such as cerebral insult and damage of coronary vessels are very rare (< 0, 5%), but a potential risk for the patient. The radiation required for a single angiogrammay cause a small increase in risk of developing cancer from 25,00% to 25.01%.

OCT does require an infusion of about 15-20 ml of contrast medium. This is a small dose, and should not pose any threat of contrast induced nephropathy for the individual with a GFR > 45. The risk is < 0,1%. Wire manipulation gives some risk for wire induced damage to the vessel, e.g. dissection and perforation, but is rare < 1%. With FD OCT patients in a minority of cases experience transient chest pain oppression during acquisition. T wave abnormalities have been observed (10%), but no major vascular complications (1).

The follow up by phone and one clinical visit cause some inconvenience for the participants.

Given the potentially benefit of the study, the risks involved are small and can be ethically justified.

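### New hospitalisation is not a seriousness criterion in section 5, so some unexpected admissions after discharge, such as a non-life-threatening bleed, are not captured as SAEs and have no stated route to the events committee

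*Protocol*

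**What the plan says.** Section 5 of the protocol opens its reporting rule with "To be reported as SAE are unexpected clinical happenings leading to" and then names three outcomes: "Life threatening incidences", "Prolonged hospitalization" and "Persistant or significant disability".

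It adds events that are always reportable: every death, "All incidences of contrast nephropathy", loss of coronary flow after stenting, "All cases of stent failure, eg stent thrombosis, stent fracture, loss of stent", and bailout DES in a BVS patient. A closing sentence takes out expected events unrelated to the stents. One of its examples is readmission where there is no sign of restenosis or stent thrombosis.

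The same section has the CEC assess SAEs, the primary endpoint and the clinical secondary endpoints. Section 2.2.7.3 lists those clinical endpoints.

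On follow-up, section 2.2.5 provides telephone contacts at 3 and 6 months and "clinical control as outpatient at 12 months with MCST and echocardiography". Section 2.6 separately describes the 12-month angiography with OCT and does not say whether it involves a hospital stay. Section 11.2 states: "The extra risk is primarily related to the control angiography". It names bleeding and haematoma at the access site as the major adverse effects.

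**The concern.** A hospitalisation criterion that covers only prolongation works during the index stay. After discharge there is normally no stay to prolong, so for most of the 12 months an admission does not make an event serious. It must qualify some other way.

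What is left out includes a harm that the protocol itself foresees. An access-site bleed that needs a bed but is neither life-threatening nor disabling fits no item. The same holds for another bleeding admission during the 12 months of dual antiplatelet therapy in section 2.4.

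The stakes are the completeness of safety reporting and its consistency between sites. The trial is multicentre and unblinded. Where the rule has to be interpreted, sites may report differently, and a low SAE count would partly reflect the definition.

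**Working it through.** The point rests on wording, so the check sets the SAE rule beside the endpoint list and follows different post-discharge admissions through both. The plan states no figure that could be reproduced.

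| Unexpected admission after discharge | SAE under section 5? | Clinical endpoint in 2.2.7.3? |
|---|---|---|
| Fatal, life-threatening or disabling | Yes | Death: yes. Others: depends on the cause |
| Contrast nephropathy | Yes, fixed list | No |
| Stent thrombosis | Yes, fixed list | Yes |
| Myocardial infarction, revascularisation or cerebral vascular event that meets no SAE item | No | Yes, so it reaches the CEC |
| Heart failure or arrhythmia | Named as expected and exempt | Yes, so it reaches the CEC |
| Bleed, neither life-threatening nor disabling | No | No bleeding endpoint is listed |

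Only the last row fails both tests. It stands for any admission that is outside the three outcomes, the fixed list and the endpoint list.

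**Access-site bleed after the control angiography.** If the angiography is done without a hospital stay, a bleed that needs a bed is a new admission and falls in the last row. If the patient is already admitted for it, a bleed that extends the stay is a prolongation and is captured. The outpatient wording in section 2.2.5 belongs to the clinical control and does not settle which case applies.

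**The closing exemption.** It can be read in two ways:

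1. It removes only those readmissions that are expected. Unexpected ones were then meant to be reported, but no criterion brings them in.
2. It classes every readmission without restenosis or stent thrombosis as expected. The bleeding admission is then excluded outright.

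Neither reading captures the event. Section 11.2 adds to the difficulty: because it foresees access-site bleeding, a site could also call such a bleed expected and so outside the rule's opening condition. Adding new hospitalisation to the criteria while leaving the exemption untouched would therefore not reliably reach this example.

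**Size.** The documents give no rate of admission. By way of illustration only, assumed rates of 5%, 10% and 20% in 120 patients give 120 × 0.05 = 6, 120 × 0.10 = 12 and 120 × 0.20 = 24 unplanned admissions of every kind. These include admissions captured by other items, so they do not measure the gap.

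**The case against.** The strongest reply is that the events that matter for comparing the devices are largely covered. Stent failure and death are always reportable. Myocardial infarction, revascularisation, cerebral events and heart failure or arrhythmia admissions go to the CEC as endpoints, and there are contacts at 3, 6 and 12 months. This stands. A reader might infer that every unexpected new admission escapes the SAE rule, or that the BVS-versus-DES safety comparison is seriously compromised. The documents support neither. What is left is mainly admissions outside the device endpoints, and the control angiography is planned in both arms.

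A second reply is that the protocol addresses readmission openly and may have left it out on purpose. That is a possible reading, but the text does not say so. The exemption is framed around expected events, and an exemption for expected readmissions has little purpose if no readmission was reportable. The passage is ambiguous, and section 11.2 gives a reason not to settle the ambiguity by excluding complications of a procedure that the study itself requires.

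A third reply is that the setting of the angiography is not stated. This is correct. It would be wrong to infer that every complication of it is a new admission, so the example is conditional. The gap for other admissions between discharge and 12 months does not depend on it.

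**Conclusion.** The point holds in a limited form. New hospitalisation is not a seriousness criterion. An unexpected post-discharge admission is not captured as an SAE, and has no stated route to the CEC, when all of these apply: it is not fatal, life-threatening or disabling; it is not on the fixed list; and it is not a listed clinical endpoint. Bleeding admissions are the clearest instance. The closing exemption makes the gap wider and the rule harder to apply consistently.

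The conclusion rests on a literal reading of section 5 and, for the access-site example, on the angiography being done without a hospital stay. The number of events affected cannot be estimated from the documents. It is a worthwhile correction to a stated safety rule. It does not affect the primary endpoint or the sample size.

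**What to change.** Two changes in section 5, made together:

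1. Replace the prolonged-stay criterion with: unplanned new hospitalisation or prolongation of an existing hospitalisation. State that the scheduled 12-month visit does not count.
2. Reconcile the closing exemption with this criterion and with section 11.2. Limit it explicitly to expected events, and state that admissions caused by the study-mandated control angiography or OCT are not exempt. The text should make clear that these admissions are reportable even though section 11.2 foresees such complications.

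The cost is an amended paragraph and a few more SAE reports for the sites and the existing CEC. No extra visits, staff or patients are needed, and treatment does not change.

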**6 Expected outcome of the study**

We expect to find no difference in the minimal flow area, or the secondary endpoints of MACE and stent failure.

